## Abstract

**Introduction:**

About 44% of Aboriginal and/or Torres Strait Islander women smoke during pregnancy compared to 12% of their general population counterparts. Evidence-based quit smoking advice received from health care professionals (HCPs) can increase smoking cessation rates. However, HCPs lack culturally appropriate smoking cessation training, which is a major barrier to provision of smoking cessation care for this population.

**Methods and analysis:**

iSISTAQUIT is a multicentre, single arm study aiming to implement and evaluate the evidence-based, culturally competent iSISTAQUIT smoking cessation training among health practitioners who provide support and assistance to pregnant, Aboriginal and Torres Strait Islander women in Australia. This project will implement the iSISTAQUIT intervention in Aboriginal Medical Services and Mainstream Health Services. The proposed sample size is 10 of each of these services (total N = 20), however if the demand is higher, we will aim to accommodate up to 30 services for the training. Participating sites and their HCPs will have the option to choose one of the two iSISTAQUIT packages available: a) Evaluation- research package b) Training package (with or without continued professional development points). Training will be provided via an online eLearning platform that includes videos, text, interactive elements and a treatment manual. A social media campaign will be conducted from December 2021 to September 2022 to raise brand and issue awareness about smoking cessation for Aboriginal and Torres Strait Islander women in pregnancy. This national campaign will consist of systematic advertising and promotion of iSISTAQUIT and video messages through various social media platforms.

**Analysis:**

We will use the RE-AIM framework (Reach, Effectiveness, Adoption, Implementation and Maintenance) to plan, evaluate and report the intervention impact of iSISTAQUIT. Effectiveness of social media campaign will be assessed via social media metrics, cross-sectional surveys, and interviews.

**Discussion:**

This innovative research, using a multi-component intervention, aims to practically apply and integrate a highly translatable smoking cessation intervention in real-world primary care settings in Aboriginal Medical Services and Mainstream services. The research benefits Aboriginal women, babies and their family and community members through improved support for smoking cessation during pregnancy. The intervention is based on accepted Australian and international smoking cessation guidelines, developed and delivered in a culturally appropriate approach for Aboriginal communities.

## Introduction

Tobacco smoking (referred to as smoking from here-on) represents the most important preventable risk factor for chronic disease in Aboriginal and Torres Strait Islander People. About 44% of Aboriginal and/or Torres Strait Islander women smoke tobacco during pregnancy compared to 12% of their general population counterparts. Serious effects from smoking in pregnancy include complications during the pregnancy and perinatal period, as well as heart disease, obesity, and diabetes, and behavioural and learning problems in children later in life [1]. Maternal tobacco smoking is the most important preventable risk factor for chronic lung disease in offspring [2–6]. Babies born to women who smoke are twice as likely to have low birth weight compared to those born to non-smoking mothers [7], However, if the mother quits smoking early in pregnancy, the low birth weight risk decreases to non-smoking levels [7, 8]. A baby exposed to smoking in utero has more than a five-fold risk of early smoking initiation, thus continuing the cycle of disadvantage [9]. Abstinence by pregnant women can be an important cornerstone for the whole family’s respiratory health, by reducing tobacco smoking in the home, and by becoming community role models [10]. Nonetheless, Aboriginal and Torres Strait Islander pregnant women currently quit at only half the rate of their non-Indigenous counterparts [8, 11].

Interventions using counselling and/or NRT in Indigenous adult smokers have been found to be effective (RR1.43), [12] but have not successfully been implemented into the Indigenous context for pregnant women. Four tobacco-related randomised controlled trials (RCTs) have been conducted among Indigenous pregnant women who smoke in Australia [13] and Alaska, [14–16]. The trial in Australia, compared brief interventions with more intensive intervention [13]. The three Alaskan trials included a feasibility trial of a multi-component intervention [14],a biomarker educational program, [15] and a community-based support program with ‘native sisters’ [16]. None of the interventions were able to demonstrate efficacy of the intervention compared to control.

iSISTAQUIT seeks to translate into practice the considerable evidence that smoking cessation counselling from health providers (HCPs) helps smokers quit smoking, and has a focus on training of HCPs [17]. In an Australia-wide study that surveyed 378 GPs and obstetricians working in mainstream and/or Aboriginal and Torres Strait Islander settings, we found clinicians lacked confidence in prescribing nicotine replacement therapy (NRT) for both pregnant Aboriginal and Torres Strait Islander and non-Aboriginal and Torres Strait Islander women. Of these HCPs, 75% agreed that training would help improve their management of smoking in pregnancy [18]. Despite 95% believing that NRT is safer than smoking, only 5–21% prescribe NRT and only 5–14% follow-up women [19]. These rates are similar to studies conducted internationally [20, 21].

There are several cultural aspects for Aboriginal and Torres Strait Islander people, related to smoking that may be important for health providers to understand when helping people quit. These include the history of European colonisation and dispossession of land, the introduction of tobacco into Aboriginal and Torres Strait Islander communities, ongoing racism, intergenerational trauma and the social norms of tobacco use in everyday life [22]. Thus, it is important that a targeted smoking cessation program prepares the health professional to be sensitive to the cultural and psychosocial context of tobacco smoking and avoid shaming women for smoking in pregnancy [23]. While tobacco smoking is largely commercial in nature by Aboriginal and Torres Strait Islander people in Australia, there are some populations that may have ceremonial reference to tobacco, such as the Yolŋu people of East Arnhem land [24] and the use of a nicotine-containing plant called pituri, that is chewed [25].

Since lack of confidence and training in culturally sensitive smoking cessation methods may prevent health providers from delivering effective smoking cessation intervention, the iSISTAQUIT program was designed to use health provider training in smoking cessation as the primary intervention, accompanied by practical resources to assist the consultation process. Another salient feature of iSISTAQUIT is its social media campaign that was co-designed with Aboriginal and Torres Strait Islander women, community and health providers to increase the reach and adoption of the program. The combination of equipping HCPs to provide culturally safe smoking cessation care, and the use of social platforms, such as Facebook and the internet is supported by our previous research that suggests that a considerable proportion of Aboriginal women use internet and Apps for their and their children’s health related needs [26]. Internationally, a social media intervention for smoking cessation is being trialled in Alaska Natives [27].

The iSISTAQUIT program has been adapted from foundation work established by a pilot project called ICAN (Indigenous Counselling and Nicotine) QUIT in Pregnancy (Phase 2) that was developed and trialled in six Aboriginal Community-Controlled Health Organisations (ACCHOS) with the aim of training HCPs in culturally sensitive smoking cessation assistance to pregnant Aboriginal and Torres Strait Islander women who smoke, [28–30] as well as the SISTAQUIT Randomised Controlled Trial (Phase 3) [31]. This is intervention built on extensive formative research into pregnant Aboriginal and Torres Strait Islander women who smoke and health professional delivery of smoking cessation care [10, 32–40]. iSISTAQUIT is the implementation phase of SISTAQUIT and is based on same principles of smoking cessation training with additional adaptions including digital innovations in online training, medical practice software and a social media campaign.

## Material and methods

iSISTAQUIT is a quasi-experimental, [41] multicentre, single arm implementation study aiming to implement evidence based culturally competent iSISTAQUIT training among health practitioners that provide support and assistance to pregnant Aboriginal and Torres Strait Islander women in Australia.

### Objectives

This research has three main objectives:

Deliver the iSISTAQUIT training intervention in Aboriginal Community Controlled Health Organisations (ACCHO’s) and in mainstream health settings that service Aboriginal and Torres Strait Islander pregnant women.Evaluate the delivery of iSISTAQUIT to services, considering process, impact and comparison between Aboriginal and Torres Strait Islander and Mainstream servicesDevelop, disseminate and evaluate a social marketing/social media campaign to motivate and aid pregnant women to quit and support health professionals in this work.

#### Ethics approvals

Ethics approvals have been obtained from Human Research Ethics Committees of University of Newcastle, Southern Cross University and Aboriginal Health and Medical Research Council. Where required, ethics approvals or ratifications have been obtained from respective states’ Aboriginal Health Research and Ethics Committee.

Current HREC approvals include:

### New South Wales

1. Southern Cross University HREC, Lismore NSW 2480 –Minimisation of Duplication Application Approval for iSISTAQUIT; Reference No. 2021/133. Approval date: 7/10/2021.2. The University of Newcastle, Callaghan NSW 2308, Reference number H-2020-0162. Approval date: 12 May 20203. Aboriginal Health and Medical Research Council (AH&MRC) Strawberry Hills NSW 2012, Reference number 1140/15. Approval date: 23/04/2020

### Queensland

4. Far North Queensland HREC, Cairns & Hinterland Health Service District, Reference number HREC/18/QCH/27. Approval date: 2/4/20205. Darling Downs Hospital and Health Service (DDHHS): Reference number HREC/18/QTDD/10. Approval date: 09-04-2020

### Northern Territory

6. Top End HREC (NT Dept of Health/Menzies School of Health Research): Reference number 2017–2997. Approval date: 23-03-2020

### Western Australia

7. Western Australian Aboriginal Health Ethics Committee: Reference number 826. Approval date: 28-04-2020

### South Australia

Aboriginal Health Research Ethics Committee (AHREC) Aboriginal Health Council of South Australia. Reference number 04-16-652.

### Inclusion criteria and recruitment of sites

ACCHO’s will be recruited through their network. We will also invite participation from the Aboriginal Medical Services (AMSs) that have been interested in the SISTAQUIT RCT (Phase 3) [42] but were not eligible to join, or declined due to the research burden, or have finished being in the control arm of the SISTAQUIT RCT. We will also invite health services taking part in the Tackling Indigenous Smoking program, and other health services that express interest.

We will explore interest among Mainstream sites that see a high volume of Aboriginal and Torres Strait Islander pregnant women, to ensure we maximise our reach to Aboriginal and Torres Strait Islander women. We will also advertise in the media, through peak organisations and social media. We will opportunistically promote the recruitment of sites via conferences and specialised meetings. The scope of Mainstream services will include General Practice and Mainstream antenatal services (usually run by Local Health Districts or similar).

Consent will be obtained from the participating services in form of written, witnessed agreements. All health providers will provide consent in an electronic, online format. Service chief executive officers (CEOs) will provide written, informed and witnessed consent through paper consent forms for interviews. No minors will be involved in the study. All consenting health providers who see a pregnant woman in the participating services will be eligible to receive the iSISTAQUIT training and training resources.

Depending on COVID-19 restrictions, sites that express interest early in the recruitment period (early adopter services) will have an option to be involved in developing and filming the creative approach, campaign messages and video materials for the social media campaign.

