*Video production*. Gilimbaa as the creative agency will conduct Community consultations (group discussions separately with Aboriginal and Torres Strait Islander women, health professionals and community leaders) to inform the creative approach and video content. Subject to pandemic and public health restrictions, it is anticipated that a series of short videos will be produced either in-house or in different locations across Australia, whichever is feasible. Key messaging in the videos will promote smoking cessation among Aboriginal and Torres Strait Islander women and families and highlight the importance of smoking cessation care, i.e., helping people and health practitioners feel confident and that it is worthwhile spending the time assisting pregnant women to quit. The videos will encourage Aboriginal and Torres Strait Islander women to seek and accept help from health providers, community, and family to quit smoking. A central Aboriginal talent will be engaged to present the iSISTAQUIT messages through short videos and bring to light community stories. Contingency plans will be made if the filming is interrupted due to travel restrictions.

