#### Outcome measures related to social media campaign

Engagement, awareness and effectiveness of the social media campaign will be measured through a combination of methods including assessment of social media metrics of online content released by the campaign as well as surveys and qualitative interviews with stakeholders including health care providers, Aboriginal and Torres Strait Islander women and community members. More details are available from Table 3.

**Table 3 pone.0274139.t003:** Evaluation of social media campaign.

Characteristic	Details
**Target population**	Aboriginal and Torres Strait Islander audience exposed to the social media campaign including pregnant women, other women of reproductive age, their family members, their social contacts, and health care providers catering to Aboriginal women in pregnancy.
**Study design**	Survey, post-survey interview/focus group and social media surveillance
**Recruitment**	Aboriginal community participants will be recruited via social media (through active calls for participation via iSISTAQUIT and collaborators’, panel members’ and supporters’ websites and social media pages), participant interception at iSISTAQUIT study sites and community events. Participants will be asked to share the survey with others, or recommend them to take the survey, through snowball recruitment.
**Sample size**	If 50% of participants have heard of the campaign in the post period, a sample of 100 women from the iSISTAQUIT sites will enable estimation of this proportion with a 10% margin of error. Sample size for qualitative interviews will depend on numbers needed to attain data saturation.

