**Data collection and outcome measures**	**Surveys:** To assess engagement, awareness and effectiveness of the social media campaign and related branding in influencing knowledge, attitudes and beliefs of pregnant women who smoke. **Qualitative interviews or focus groups:** conducted after about 3–6 months of campaign initiation with women, community members and Health Providers. A semi-structured interview schedule will be used to steer the interview/focus group discussion. Below are some examples of the questions included in the schedule: • What did you like about the campaign? What are we doing well? What should we continue to do? • What are we doing okay or badly with the campaign? • What we could have done instead? • Do you have any likes/dislikes / suggestions about the videos? • Have the videos changed your views or behaviour in any way? • Did you learn anything new? **Both surveys and interviews will be conducted together via personal intercept at the study sites.** **Social media metrics:** Social media metrics will be directly tracked and recorded from the social media webpages using platform specific social media tracking. IndigenousX will deliver these metrics in a detailed report. This will demonstrate the effectiveness of the campaign with the intended audience and the public. Google analytics will be used to profile the characteristics of the audience. Following metrics will be summarised both overall and by month: **Engagement**: Counts of retweets, likes, comments, link clicks, mentions, and direct messages received. **Content sharing**: Counts of testimonials, shares, reviews, guest posts, shared pictures at monthly intervals throughout the campaign **Audience characteristics**: Counts of total followers, new followers. This will also be broken down by users’ sex and age and location (Google analytics). **Content utilisation:** a) analysing comment sentiments (positive, neutral, or negative as supplied by IndigenousX), b) summary statistics of website utilisation will be presented, including the number of website sessions, total page views, bounce rate (single-page sessions divided by the number of total sessions on the website), pages per session, average session duration, mobile vs. desktop traffic.

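### Respondents who helped make the social media campaign are not identified in its evaluation, so awareness and opinion may be biased upward by an unknown amount

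*Protocol article*

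**What the plan says.** **Making the campaign.** The section on inclusion criteria and recruitment of sites offers early-joining sites a role in production: "early adopter services) will have an option to be involved in developing and filming the creative approach, campaign messages and video materials". The offer is conditional: "Depending on COVID-19 restrictions, sites that express interest early in the recruitment period". The Introduction describes the campaign as already co-designed with women, community and health providers. Under Social media campaign, the video production text has the creative agency hold "group discussions separately with Aboriginal and Torres Strait Islander women, health professionals and community leaders", without saying whether these people come from study sites. The Governance section has a Social Media Panel guiding the campaign.

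**Evaluating the campaign.** Table 3 defines the target population as "Aboriginal and Torres Strait Islander audience exposed to the social media campaign including pregnant women, other women of reproductive age", and goes on to include family, social contacts and health care providers. Recruitment runs through the project's own pages and those of collaborators, panel members and supporters, through "participant interception at iSISTAQUIT study sites and community events", and by snowballing. The setting is given as follows: "Both surveys and interviews will be conducted together via personal intercept at the study sites". On sample size, assuming 50% have heard of the campaign, "a sample of 100 women from the iSISTAQUIT sites will enable estimation of this proportion with a 10% margin of error". The sample interview questions ask women, community members and providers what they liked, what is going well and what is going badly. Survey responses are to be summarised descriptively. Table 3 states no exclusion, flag or separate display for people who helped make the campaign.

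**The concern.** The pool of sites that may help produce the campaign is also the pool that supplies respondents to judge it. Someone who joined a consultation, helped shape a message or appeared in a video has almost certainly heard of the campaign, but not because it was distributed on social media. That person also has a stake in its success and is more likely to speak well of it.

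Two results are exposed. One is the awareness proportion among women, which is the only campaign estimate that the article sizes. The other is the opinion material from women, community members and providers. If contributors cannot be told apart in the data, the effect cannot be bounded afterwards. Recruiting through panel members' and supporters' pages adds a further route by which people close to the campaign enter the sample.

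**Working it through.** **1. Reproduce the stated margin.** Inputs from Table 3: n = 100 women, p = 0.50. The confidence level is not stated; 95% is assumed, with simple random sampling.

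Half-width = 1.96 × √(0.50 × 0.50 / 100) = 0.098, or 9.8 points. The stated 10% is reproduced (97 women would be enough). This figure measures sampling error only and says nothing about who the respondents are.

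**2. What contributors could add.** Let s be the share of surveyed women who helped make the campaign and a their awareness. Keep 50% for everyone else, as in Table 3. Then

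expected awareness = (1 − s) × 0.50 + s × a, so bias = s × (a − 0.50).

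The documents give neither s nor a. Both are assumptions, shown over a range.

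| s | bias, a = 70% | bias, a = 90% | bias, a = 100% |
|---|---|---|---|
| 2% | 0.4 points | 0.8 points | 1.0 points |
| 5% | 1.0 points | 2.0 points | 2.5 points |
| 10% | 2.0 points | 4.0 points | 5.0 points |
| 20% | 4.0 points | 8.0 points | 10.0 points |

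**3. When the bias would match the margin.** Setting s × (a − 0.50) = 0.098 gives s = 0.098 / 0.50 = 19.6% for a = 100%, 0.098 / 0.40 = 24.5% for a = 90%, and 0.098 / 0.20 = 49% for a = 70%. Contributors would have to make up about a fifth of the sample or more.

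**4. What excluding contributors costs.** Half-width = 1.96 × √(0.25 / m), where m is the number of women left. To keep 100 uninvolved women, recruit 100 / (1 − s), rounded up.

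| Share excluded | Women left | Half-width without replacement | Recruits needed to keep 100 |
|---|---|---|---|
| 5% | 95 | 10.1 points | 106 |
| 10% | 90 | 10.3 points | 112 |
| 20% | 80 | 11.0 points | 125 |

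**5. Opinion data.** No arithmetic applies. Providers and community members are interviewed and belong to the groups named as co-designers, so the overlap is possible here too. Providers do not enter the 100-woman proportion.

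**The case against.** The strongest reply is that the overlap may be small or absent. Site involvement is optional and depends on COVID-19 restrictions. The article also allows the videos to be produced in-house, and it does not place the consultation participants at study sites. The offer is made to services, and a woman who attends such a service is not thereby a maker of the campaign. All of this stands. It limits the point to a possible bias of unknown size.

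A second reply is that an article condenses a fuller protocol, and a screening item may sit in the questionnaire. That is fair, and if the item exists the point is already met. But Table 3 does set out target population, recruitment, sample size, setting and analysis, and those stated choices create the overlap. The Data collection section gives the end-of-study interviews to an external agency to avoid bias; no comparable protection is stated for the campaign survey.

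A third reply is that Table 3 counts having heard of the campaign by any route, so word of mouth is legitimate awareness. This holds for ordinary contacts. It does not hold for contributors, whose awareness is all but assured by taking part and so is no evidence of the campaign's reach. The interview schedule does invite criticism as well as praise, but that does not reveal who is speaking.

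A reader might go further and want filming sites left out of the headline figure. The documents do not support that. The campaign's distribution is focused on the early-adopter states, so leaving out those sites could remove women in the areas of heaviest promotion and understate awareness. A gap between filming and other sites would mix real exposure with participation.

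**Conclusion.** The point holds as a possible upward bias with a cheap remedy. The plan lets people who helped make the campaign be counted as evidence of its reach and appeal, and states no means of identifying them. The size cannot be derived from the documents. As an illustration, it is 1 to 5 points on awareness if 2% to 10% of surveyed women were involved, all of them were aware, and awareness is 50% otherwise. It would match the 9.8-point margin only at about 20% involvement.

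Two stronger readings should not be drawn. A reader might infer that awareness is overstated and that the campaign is rated by its makers. The documents show only that this can happen, since the number of contributing sites and people is not given. A reader might also infer that providers who helped with messages start the training surveys from a raised baseline. Nothing in the article places providers' campaign work before their pre-training survey or shows that it overlaps with what that survey asks.

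**What to change.** Add one item to the Table 3 survey and interview: did the respondent take part in campaign consultations, development or filming? Take the headline awareness proportion from women who did not. Show awareness and opinion results with and without contributors. Results by site can be displayed descriptively, but no site needs to be removed from the headline.

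The cost is one question and one extra set of descriptive results. If 5% to 20% of women are excluded without replacement, the margin widens by about 0.3 to 1.2 points; recruiting 106 to 125 women instead of 100 avoids that loss.
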